#### 11.4.2 Primary Analysis

The primary outcome (time in target at the end of ICU stay) will be compared between the two groups using Student t test or Mann-Whitney nonparametric test, in case of non-normal distributions. Primary analysis will be done using linear regression with time in target as the dependent variable, the study arm as the main independent variable, and stratification variables (APACHE II categories and diabetic status) included as covariates (ref Points to consider on adjustment for baseline covariates. EMEA Agency, 2003). We will conclude superiority of the GS2 intervention, compared to the control or historical control groups, if the time in target is significantly higher ( $p < 0.05$ ).

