|------------------------------------|-----------------------------------------------------------------------------------------------------------------------------------------------------------------------------------------------------------------------------------------------------------------------------------------------------------------------------------------------------------------------------------------------------------------------------------------------------------------------------------------------------------------------------------------------------------------------------------------------------------------------------------------------------------------------------------------------------------------------------------------------------------------------------------------------------------------------------------------------------------------------------------------------------------------------------------------------------------------------------------------------------------------------------------|
| Statistical considerations: | 
Continuous variables will be presented according to the study group by their mean <math>\pm</math> standard deviation (SD), median, interquartile range and range. Categorical variables will be presented according to the study group by their frequencies and relative proportions. The primary outcome (time in target) will be compared between the three arms using Student t test or Mann-Whitney nonparametric test, if distributions is non-normal. For secondary outcomes, continuous variables will be compared between the three study groups using either Student t test or Mann-Whitney nonparametric test; categorical variables will be compared using either Chi-2 test, or Fischer exact test, depending on application criteria. Count data (number of hyperglycemic episodes) will be compared using Poisson regression model or negative binomial regression, if over-dispersed.
 
Significance level is set for a p-value of 0.05. All analyses will be performed using STATA IC 15.0 software.
 |

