## 11. STATISTICAL METHODS

### 11.1 Hypothesis

The null hypothesis is that the mean time in target glycaemia (defined as BG between 5 and 8.5 mm/L) will be equal between patients randomized in the intervention arm and in the standard of care arm (control group).

Alternative hypothesis is that the mean time in target glycaemia will be different between patients randomized into the intervention group and into the standard of care group (control group).

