### 11.2 Determination of Sample Size

Based on data collected routinely at the ICU between January and March 2017, the time in target was 68% (SD 21%) for patients under the standard of care. Expecting the intervention to give an improvement of 10% of time in target, we would need 71 patients in each patient group to detect give the trial a power of 80% and an alpha error of 5% (two-sided). If the patient refuses to participate afterwards or withdraws from the study for whatever reason, they will be replaced in order to have 71 per group at the end of the study.

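### Section 11.4.2 labels an adjusted regression the primary analysis but does not tie the p<0.05 rule to it, and the synopsis names a different test

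*Protocol*

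**What the plan says.** Protocol section 11.4.2 makes three statements in turn:

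- The primary outcome "will be compared between the two groups using Student t test or Mann-Whitney nonparametric test, in case of non-normal distributions".
- The sentence that follows gives a second method and labels it: "Primary analysis will be done using linear regression with time in target as the dependent variable". That model has a term for arm and adjusts for both factors used to stratify randomisation.
- Superiority is concluded if time in target is significantly higher at p<0.05. The test that supplies this p-value is not named.

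The synopsis, under statistical considerations, says the primary outcome "will be compared between the three arms using Student t test or Mann-Whitney nonparametric test, if distributions is non-normal". It does not mention the regression.

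Three other sections bear on the choice. In section 11.1 "The null hypothesis is that the mean time in target glycaemia" is equal in the intervention arm and the standard-of-care arm. Section 11.2 sizes the trial on a difference in means. Section 6.2.1 randomises 1:1 in blocks, stratified by APACHE II (three levels) and diabetic status (two levels).

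**The concern.** Two methods are attached to the primary outcome in one paragraph, and the synopsis carries only the one that section 11.4.2 does not label primary. An analyst could follow either place and contradict the other. This is a conflict inside the protocol, so it is not a detail left for an analysis plan to fill in.

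The methods are not interchangeable. They differ in what they test (means or ranks), in whether they use the stratification, and in whether they estimate the difference that sized the trial. The trial is unblinded (section 6.1), and section 11.4.5 lets methods be replaced during the analysis if they prove unsuitable. Which test decides should therefore not be open when the results are known. At stake is the main conclusion in those trials where the tests fall on opposite sides of 0.05.

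**Working it through.** **Inputs from the protocol.** Section 11.2 gives the control figures: "the time in target was 68% (SD 21%) for patients under the standard of care". The effect assumed for sizing is an absolute gain of 10 points, and the stated result is that "we would need 71 patients in each patient group", at power 80% and two-sided alpha 5%. Section 6.2.1: stratified 1:1 randomisation.

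**Assumed, because the protocol does not give them.** Share of outcome variance explained by the strata: R² = 0, 0.1 or 0.3. Stratum shares: 30/40/30% for APACHE II and 30% diabetic. Outcome shape: normal, or beta on 0 to 100% (for the beta, R² is on the underlying normal scale). Normality check: Shapiro-Wilk.

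**1. The stated sample size.** n = 2(1.96 + 0.842)² × 21² / 10² = 2 × 7.85 × 4.41 = 69.2, so 70 per group. The noncentral-t version gives 71, with power 80.4%. The 71 is thus the size for an unadjusted t test on a 10-point difference in means. A relative 10% (6.8 points) would need 150, so only the absolute reading reproduces 71.

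**2. What each method addresses.** The regression tests and estimates a mean difference, which matches sections 11.1 and 11.2. Mann-Whitney compares rank order; it does not test equal means or estimate that difference. How often the synopsis rule would switch to it depends on shape. The upper bound lies (100 − 68)/21 = 1.5 SD above the mean, so an exact normal shape is not possible. Under the beta shape, Shapiro-Wilk rejected normality in at least one arm in over 99% of simulated null trials; under the normal shape, in 9 to 10%.

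**3. Level of the unadjusted tests under stratified allocation.** With balanced strata, the variance of the mean difference is (1 − R²) × 2σ²/n, while the t test uses about 2σ²/n. Its level is therefore about 2[1 − Φ(1.96/√(1 − R²))]:

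- R² = 0.1: 1.96/0.949 = 2.07, level 3.9%
- R² = 0.3: 1.96/0.837 = 2.34, level 1.9%

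Simulation under the null (71 per arm, 60,000 trials per row, permuted pairs ordered by stratum as an approximation to the protocol's blocks; standard error of a 5% rate √(0.05 × 0.95/60,000) = 0.09 points):

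| Shape, R² | t | Mann-Whitney | Regression | Regression or Mann-Whitney | Best of three |
|---|---|---|---|---|---|
| Normal, 0 | 4.9% | 4.9% | 4.9% | 5.9% | 5.9% |
| Normal, 0.1 | 3.9% | 4.0% | 5.1% | 5.6% | 5.6% |
| Normal, 0.3 | 1.9% | 2.0% | 4.9% | 5.0% | 5.0% |
| Beta, 0 | 5.0% | 5.0% | 5.0% | 6.0% | 6.1% |
| Beta, 0.1 | 3.9% | 3.9% | 4.9% | 5.5% | 5.5% |
| Beta, 0.3 | 2.0% | 2.1% | 4.9% | 5.1% | 5.1% |

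The largest excess of best-of-three over the regression is 6.05 − 4.99 = 1.06 points. A smaller run (8,000 trials per row) had one row, normal with R² = 0, at 6.7% for best of three. The regression itself stood at 5.8% in that row, so the excess was again about 0.9 points.

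**4. Disagreement when the effect is real.** 4,000 trials with a 10-point shift, R² = 0.1, comparing the normality-switched t/Mann-Whitney with the regression:

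- Beta, values capped at 100%: switched test significant in 81.8%, regression in 80.0%, both in 78.0%. Disagreement (81.8 − 78.0) + (80.0 − 78.0) = 5.8%.
- Normal: 80.4%, 83.2% and 80.1%. Disagreement 0.3 + 3.1 = 3.4%.

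Further runs with blocked stratified allocation gave about 4.5 to 5%.

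**The case against.** The strongest reply is that section 11.4.2 does designate one analysis. Only the regression is called primary, its outcome, arm term and covariates are given, and the p<0.05 sentence follows it directly. On that reading the t test or Mann-Whitney is a preliminary unadjusted comparison. This stands in part. A reader might infer that no single test lies behind the decision, and the label rules that out. It does not settle the matter, because the decision sentence still names no test and the synopsis gives only the other method.

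A reader might also infer that the trial's error rate is not 5%. The documents do not support that. The labelled test holds about 5%, the unadjusted tests are at or below 5%, and even choosing the best of three after the fact gives about 5 to 6%. Best-of-three rates of 7.6 to 7.9% appear only if allocation is simulated as simple randomisation, which section 6.2.1 excludes.

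Three further replies are fair. The synopsis's three-arm wording is loose rather than impossible, since section 11.4.1 sets out pairwise comparisons. The near-certain switch to Mann-Whitney rests on an assumed shape and an assumed normality test. Ordinary regression keeps its level in these simulations, so there is no case here for requiring robust standard errors.

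**Conclusion.** The point holds as a contradiction over the primary test. Section 11.4.2 labels the adjusted regression primary, keeps a second method for the same outcome, and ties p<0.05 to neither; the synopsis names only the second method. That method can leave the stated null hypothesis. It is also conservative under stratified randomisation: about 2 to 4% in place of 5% if the strata explain 10 to 30% of the variance.

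The cost is not large alpha inflation, which is at most about one point. It is that, with a true 68% v 78%, roughly one trial in twenty (3 to 6% over the shapes tried) would have two protocol-supported answers that disagree. These sizes rest on the assumed strata strength, stratum shares and outcome shape; the contradiction rests on the text alone. The superiority sentence also admits the historical group as a comparator. That is a separate question and enters none of these figures.

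**What to change.** In section 11.4.2 and the synopsis, name one primary test: linear regression of time in target on randomised arm (intervention against randomised control, as in section 11.1), with APACHE II category and diabetic status as covariates. State that the p<0.05 superiority rule refers to the arm coefficient of this model, and report the adjusted mean difference with its 95% confidence interval. Keep the t test and Mann-Whitney, if wanted, as supportive analyses that cannot change the conclusion.

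The cost is protocol wording only. The sample size stays at 71 per arm: it already covers an unadjusted t test, and adjustment does not reduce power (normal outcome, R² = 0.1: 83% adjusted against 81% for the t test).

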| Measurements and procedures: | 
Screening will be done every day (Monday to Friday). Eligible patients will be randomly allocated to either intervention or control group. Before inclusion, all patients will be treated according to the ICU- Geneva Protocols.
 
Collected data:
 
Baseline at study inclusion day
 
 
- Body mass, height and body mass index (BMI)
 
- Age, gender
 
- Date and time of admission in the ICU
 
- Primary diagnostic
 
- Known chronic illness (diabetes, acute kidney injury (AKI), pancreatitis, tumor, etc.).
 
- Medication influencing glycaemia (oral antidiabetics' insulin, steroids, prednisone, etc.).
 
- Renal and hepatic status
 
- Glycaemia and lactate
 
- Vitals
 
- Severity score (APACHE II, SAPS II) at ICU admission
 
 
Daily data from inclusion day (maximum follow up of 15 days)
 
When possible – Following routines measurement.
 
 
- Glucose measurements
 
- Other laboratory: lactate, CRP, sodium (Na), potassium (K), glycohemoglobin (HbA1C), urea, creatinine, glomerular filtration rate (GFR), protein, albumin, ASAT, ALAT, phosphatase alkaline, γ-glutamyltranspeptidase (GGT), bilirubin
 
- Any events (intubation, extubation, length of surgery, infusions, cardiac events, infections, requirement for red blood cell (RBC) transfusion, hemodynamic rate (HR), organ failure)
 
- Vitals (blood pressure, temperature, heart rate etc.)
 
- Antibiotics usage
 
- Vasopressor
 
- Steroids
 
- Propofol® for sedation
 
- Glucose perfusion
 
- Insulin therapy including boluses.
 
- Body weight, BMI, Ideal body weight (if needed), presence of oedema.
 
- Energy expenditure (IC or predictive formula)
 
- Energy and protein targets over the day
 
- Prescription and administration (ml of product, kcal and grams of protein).
 
- Daily water balance
 
- Diuresis
 
- Diarrhoea, constipation
 
- Nausea, Vomiting, gastric residual
 
- Physical therapy
 
- Medical Research Council Scale (MRC Scale)
 
 
Upon ICU leave
 
 
- Duration of ICU stay
 
- MRC Scale at ICU discharge
 
- Alive status at ICU discharge
 
- Duration of hospitalization
 
- Alive status at hospital discharge
 
- BMI at hospital discharge
 
 |

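### The primary regression leaves out baseline glycaemia, which the trial already collects; the planned model is valid, but precision is forgone for the price of one degree of freedom

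*Protocol*

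**What the plan says.** Section 11.4.2 names the terms of the primary model: study arm, plus "stratification variables (APACHE II categories and diabetic status) included as covariates". No other covariate is mentioned. Section 11.4.3, by contrast, leaves room for further prespecified variables in the secondary models without naming them. The covariates match the randomisation in section 6.2.1, which is 1:1 and stratified by three APACHE II bands and by diabetes yes/no.

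The synopsis, under the baseline data for the day of inclusion, lists "Glycaemia and lactate". Section 7.1 requires at least one glucose reading of 10 mmol/l or more, or two of 8.5 mmol/l or more, so a reading exists before randomisation for every patient. The investigation schedule, however, ticks its glycaemia row only in the intervention column and not at Visit 1, although laboratory tests are ticked there.

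Section 5.1 defines the outcome. Each glucose value is carried forward to the next, time within 5.0 to 8.5 mmol/l is summed, and the denominator runs from the first reading until two hours past the final one. It does not say whether that first reading comes before or after randomisation.

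Section 11.2 bases the sample size on routine data in which "the time in target was 68% (SD 21%) for patients under the standard of care", an "improvement of 10% of time in target", and "71 patients in each patient group". It claims no gain from covariates.

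**The concern.** Under section 5.1, time spent above 8.5 mmol/l counts against the patient from the start of the clock. A patient who starts high can therefore be expected to lose some time in target while glucose comes down. In a 72 h window, 7.2 h out of range costs 10 percentage points (7.2/72), which is the whole planned effect. In a 15-day window the same 10 points takes 36 h (36/360). Section 7.2.1 has patients treated under local protocols before inclusion, so starting values can be expected to differ between patients.

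If baseline glycaemia predicts time in target beyond what APACHE II band and diabetic status already explain, leaving it out keeps explainable variation in the error term. The sample size has almost no reserve: at 71 per arm, power is 80.4%. What is at stake is a wider confidence interval and somewhat lower power than the same patients could give. The validity of the comparison is not at stake.

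**Working it through.** **Inputs from section 11.2.** Two-sided alpha 0.05; power 80%; SD 21 points; difference 10 points (absolute reading); 71 per arm. There is no inflation for dropout, because for patients who withdraw "they will be replaced in order to have 71 per group at the end of the study".

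**Assumed input.** r is the partial correlation of baseline glycaemia with time in target, given APACHE II band and diabetic status. The protocol does not give it, so a range of 0.1 to 0.5 is shown. The unadjusted SD of 21 serves as the reference, as if the two stratification factors explained nothing.

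**Step 1: reproduce the plan's figure.** Normal approximation: n = 2 × (1.960 + 0.842)² × 21² / 10² = 69.2, so 70 per arm. With the t distribution, n = 70.2, so 71 per arm, which matches the protocol. Power at 71 per arm is 81.0% (normal) or 80.4% (t). Reading the 10% as relative (6.8 points) would need 150 per arm by the normal approximation, so the absolute reading is the one the protocol used.

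**Step 2: add the covariate.** Residual SD = 21 × √(1 − r²). SE of the difference = residual SD × √(2/71). Power comes from the two-sample t test with noncentrality 10/SE.

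| Assumed partial r | Variance removed (r²) | Residual SD | SE of difference | Power at 71 per arm | n per arm for 80% power |
|---|---|---|---|---|---|
| 0 | 0% | 21.0 | 3.53 | 80.4% | 71 |
| 0.1 | 1% | 20.9 | 3.51 | 80.8% | 70 |
| 0.2 | 4% | 20.6 | 3.45 | 82.0% | 68 |
| 0.3 | 9% | 20.0 | 3.36 | 84.0% | 64 |
| 0.4 | 16% | 19.2 | 3.23 | 86.7% | 60 |
| 0.5 | 25% | 18.2 | 3.05 | 90.2% | 53 |

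The gain is therefore worth 1, 3, 7, 11 or 18 patients per arm as r goes from 0.1 to 0.5.

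**Step 3: cost.** The planned model has five coefficients (intercept, arm, two for APACHE II, one for diabetes), which leaves 142 − 5 = 137 residual degrees of freedom. One more covariate leaves 136. The factor 137/136 = 1.007 is a cost of about 0.7% of the variance, so the gain and the cost are close to even at r = 0.1 (1% removed).

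**The case against.** The strongest reply is that nothing in section 11.4.2 is wrong. Adjusting for the factors used to stratify is sound, the randomised comparison is unbiased, and the stated power is reached without another covariate. All of that stands.

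The gain may also be small. Entry requires hyperglycaemia, which restricts the range of starting values. Diabetic status, already in the model, may carry part of the same information. The outcome is averaged over as much as 15 days. In the first predecessor pilot described in section 3.3.3, nine of ten patients reached that study's target range after a mean of 5 h, which is about 7% of 72 h (5/72) and 1.4% of 15 days (5/360). These are good reasons not to rely on the upper end of the range of r. They do not remove the case for the covariate, because it costs so little.

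A further reply is that extra covariates can be left to a statistical analysis plan. Here the protocol names the primary covariates itself. Section 11.4.5 allows other methods if the planned ones prove unsuitable during analysis, which is not prespecification.

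Three stronger readings are tempting, and the protocol does not support them:

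- A reader might infer that chance imbalance in starting glucose biases the primary result. Under randomisation, such imbalance is already reflected in the standard error and p-value.
- A reader might infer that time in target is fixed by the starting glucose, so that a large loss of power is certain. Neither the correlation nor the spread of inclusion values is given, so the size cannot be claimed.
- A reader might infer that the APACHE II bands should give way to the continuous score, since the synopsis records "Severity score (APACHE II, SAPS II) at ICU admission". That would remove from the model the factor actually used to stratify, and no gain from it has been shown.

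**Conclusion.** Baseline glycaemia should be in the primary model as a low-cost gain in precision. That it is omitted, that a value is available for every patient, and that the likely direction of benefit is favourable all follow from the protocol. The size does not. Power at 71 per arm would rise from 80.4% to between 80.8% (partial r 0.1) and 90.2% (partial r 0.5), with r assumed and 21 points as the reference SD. If the stratification factors already explain part of the variance, the planned model's power is somewhat above 80.4% and the further gain in power points is smaller.

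These figures apply to the randomised comparison only. The comparison with historical controls in section 11.4.2 is not randomised. There the covariate would bear on confounding, which is a separate question not sized here.

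**What to change.** - In section 11.4.2, keep APACHE II category and diabetic status, and add the last glucose value before randomisation as a continuous covariate. Fix this before any comparison of outcomes by arm.
- In section 5.1, state that the time-in-target clock starts after randomisation, so that the covariate lies outside the outcome window.
- In the investigation schedule, align the glycaemia row at Visit 1 with the synopsis, which lists it as baseline data.

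The cost is a few sentences, one schedule entry and one degree of freedom. No additional patients or procedures are needed, because the value is already part of the inclusion data.

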| Design:                         | 
Randomized controlled study with an intervention group, a control group; a historical control group will also be studied:
 
 
- Intervention group: Glucosafe 2 is used until the patient is discharged from the ICU or for a maximal follow-up of 15 days or when he/she starts eating (voluntary feeding). Number of patients: 71
 
- Control group: Standard care according to local ICU protocols (Geneva-HUG). The maximal follow-up is of 15 days or when he/she starts eating (voluntary feeding). Number of patients: 71.
 
- Historical control group: retrospective data from a random sample of 71 patients exposed to the standard care regarding nutrition support and glycaemic control and recruited before the beginning of the pilot study in order to minimize the “cross-over” effects and to confirm the predictive accuracy of Glucosafe2. Historical controls’ data will be retrospectively harvested from the patients’ computerized record. They will be recruited within 2 years before the trial start.
 
 |
| Inclusion / exclusion criteria: | 
Inclusion criteria:
 
All patients <math>\geq 18</math> years old admitted in adult ICU- Geneva with
 
 
• An expected length of stay <math>\geq 72</math>h
 
• At least 1 blood glucose (BG) measurement <math>\geq 10</math> mmol/l or 2 BG measurement <math>\geq 8.5</math> mmol/l
 
• Informed Consent signed by the subject/ legal representative, except for patients in the historical control group
 
 
Exclusion criteria:
 
 
• Lack of legal consent or consent withdrawn, except for patients in the historical control group
 
• Pregnant or breast feeding
 
• Diabetic ketoacidosis or hyperosmolar state
 
• Oral feeding
 
• Fulminant hepatic failure
 
• Medically contraindicated to receive rapidly acting insulin by intravenous (iv) infusion or iv injection
 
                                                                                                                                             |

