#### 7.2.2 Historical control group

The patients in the historical control group will be recruited retrospectively as consecutive eligible patients, beginning within 2 years before the start of the recruitment into the intervention and the control groups.

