#### 11.4.1 Datasets to be analysed, analysis populations

The dataset from intervention group will be analysed against both the control group and the historical control group. To assess a possible “cross-over” effect, the control group will be analysed against the historical control group. All analyses will be performed in an intention-to-treat basis: all patients will be analysed as randomized.

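### Section 11.4.2 allows a claim of GS2 superiority over either the randomised or the historical control at p<0.05, without requiring the randomised comparison to succeed

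*Protocol*

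**What the plan says.** Protocol 11.1 states one null hypothesis: mean time in target "will be equal between patients randomized in the intervention arm and in the standard of care arm (control group"). Section 11.2 plans 71 patients per group for "a power of 80% and an alpha error of 5% (two-sided"), from a standard-care mean of 68%, an SD of 21% and an improvement of 10%.

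Section 11.4.2 opens by comparing two groups and names a linear regression adjusted for APACHE II category and diabetic status as the primary analysis. It ends: "We will conclude superiority of the GS2 intervention, compared to the control or historical control groups, if the time in target is significantly higher", at p<0.05.

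Other places bring in the third group:

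- Section 11.4.1: "The dataset from intervention group will be analysed against both the control group and the historical control group".
- Synopsis, statistical considerations: "The primary outcome (time in target) will be compared between the three arms using Student t test or Mann-Whitney nonparametric test".
- Synopsis, objectives: the primary objective compares time in target across three groups, one of them historical.

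Section 3.6 includes the historical group so that a cross-over effect on the control arm can be assessed. Section 6.1 repeats that purpose and adds confirmation of GS2's prediction accuracy. The group is retrospective, not randomised, and drawn from the 2 years before the trial.

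**The concern.** The closing sentence of 11.4.2 joins the two comparators with *or*. Nothing in the protocol ranks them, divides alpha between them or makes the historical comparison depend on the randomised one. A superiority statement could therefore come out of the primary analysis although GS2 did not beat its randomised control.

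Two things are at stake. First, a second test at an unadjusted 5% gives a second chance of a favourable result. Second, and more important, the contrast with historical patients mixes the effect of the device with differences between periods and between selected populations. An alpha adjustment does not separate these.

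**Working it through.** **Inputs.** From 11.2: SD 21, difference 10 (taken as percentage points), 71 per group, alpha 5% two-sided, power 80%. From 11.4.1: two comparisons that share the GS2 arm. Drift between periods is an assumption, shown as a range.

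**Step 1: the plan's own figure.** For one two-group comparison, n = 2 × (1.96 + 0.84)² × 21² / 10² ≈ 69.1, so 70 per group by the normal approximation. The t-based solution is 70.2, rounded up to 71. This reproduces the stated 71. Power at 71 is 80.4% (t) or 81.0% (normal). The sample size therefore belongs to a single comparison at an unadjusted 5%.

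**Step 2: standard error and correlation.** SE of a difference = 21 × √(2/71) = 3.52 points. With equal groups and one shared arm, the two z-statistics have correlation (21²/71) / (2 × 21²/71) = 0.5.

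**Step 3: no GS2 effect, no drift.** A favourable result is z > 1.96 in either comparison. From the bivariate normal with correlation 0.5, 1 − P(both ≤ 1.96) = 4.5%, against 2.5% for one comparison. Counting either direction, the scale on which alpha is stated, it is 9.1% against 5%.

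**Step 4: no GS2 effect, upward drift of d points.** The randomised z keeps mean 0 and the historical z has mean d/3.52.

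| Assumed drift (points) | Favourable versus historical | Favourable by either route |
|---|---|---|
| 0 | 2.5% | 4.5% |
| 1 | 4.7% | 6.5% |
| 3 | 13.4% | 14.6% |
| 5 | 29.4% | 30.0% |
| 10 | 81.0% | 81.0% |

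Example for d = 3: P(Z > 1.96 − 3/3.52) = P(Z > 1.11) = 13.4%. Downward drift works the other way: the either-route figure falls from 4.5% towards the 2.5% of the randomised test alone.

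**Step 5: would an alpha split help?** Testing each comparison at 0.025 brings the no-drift figure to 2.3%. It needs 84 per group for 80% power, or leaves 72.4% at 71. With 5 points of assumed drift, the chance of a favourable result by either route is still 20.9%.

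**Step 6: power under the rule as written.** At a true effect of 10 points and no drift, at least one favourable result has probability 91.9%, against 81.0% for the randomised comparison alone. The either-route reading is not the rule that 71 was calculated for.

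**Step 7: non-comparability visible in the protocol.** Section 2.7.1 says that leaving out patients whose consent cannot be obtained would cause selection bias. It asks for historical data to be used without consent, apart from documented refusals. Prospective patients need consent, and under the same section their data are destroyed on refusal or if no proxy consent is found. Section 7.2.1 screens Monday to Friday and gives priority to patients whose relatives can be reached first. These filters apply to both randomised arms but not to the historical group. Adjustment for APACHE II category and diabetic status covers imbalance in those two factors only.

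**The case against.** The sentence in 11.4.2 can be read comparator by comparator: superiority over control if that test is significant, and superiority over the historical group if that one is. Section 11.1, the opening of 11.4.2 and the sample size all point to the randomised comparison as the main one, and no passage defines a positive trial. This stands in part. A reader might infer that the protocol adopts a single success rule under which either comparison makes the whole trial positive; the text permits that reading but does not state it. The defect remains on the milder reading, because the primary analysis would still declare superiority over a non-randomised group, whatever the randomised result.

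A reader might also infer that the protocol excludes the historical group from any efficacy role. It does not. Sections 3.6 and 6.1 give two other purposes, but the synopsis objective and sections 3.5 and 11.4.1 list the group among the efficacy comparisons. The document contradicts itself on this.

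The inflation from multiplicity alone is modest, and that stands. The drift figures should not be read as loss of Type I error in the historical test: under drift the two means do differ, and the error lies in crediting the difference to the device. Nor do the documents show that drift occurred.

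One could argue that the historical comparison is needed because contamination may dilute the randomised contrast. Supportive estimates can show such a pattern without a superiority claim, though they cannot separate contamination from drift or selection.

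**Conclusion.** The point holds. The superiority rule in 11.4.2 conflicts with the hypothesis in 11.1, the sample size in 11.2 and the purposes of the historical group in 3.6 and 6.1, and the synopsis adds to the conflict. It allows a superiority claim against patients who were not randomised and were treated up to 2 years earlier, even if the randomised comparison fails.

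The unadjusted second comparison takes the chance of a favourable false result from 2.5% to 4.5% (two-sided, 5% to 9.1%), assuming normal statistics, equal SDs and 71 per group. The main issue is bias: 6.5% to 81% by either route across an assumed upward drift of 1 to 10 points. That range illustrates sensitivity and is not an estimate for this unit.

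The sampling of the historical group is also described in two ways: "retrospective data from a random sample of 71 patients exposed to the standard care" in the synopsis and "will be recruited retrospectively as consecutive eligible patients, beginning within 2 years before the start" in 7.2.2. This is a separate inconsistency and adds nothing to the weight of the present point.

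**What to change.** - **11.4.2:** replace the last sentence with: superiority of GS2 will be concluded only if the covariate-adjusted regression shows higher mean time in target in the GS2 arm than in the randomised control arm, with two-sided p<0.05.
- **11.4.1:** state that GS2 versus historical and control versus historical are supportive, reported as adjusted differences with 95% confidence intervals and no superiority claim. State also that analysis as randomised applies to the two randomised arms.
- **Synopsis:** limit the primary objective and the primary test to the two randomised arms, in line with 11.1, and move the historical group to the supportive comparisons.
- **Separately:** give one sampling rule for the historical group in the synopsis and 7.2.2.

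No patients are added, and 71 per arm keeps 80.4% to 81.0% power at the stated alpha. The sponsor gives up one route to a positive claim. The change concerns the primary decision rule, so it may count as a substantial amendment, which under section 2.10 needs ethics committee and authority approval before it takes effect.
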